### Screening and demographics

All participants will be asked to provide data at the beginning of their application regarding their age, sex, education level, living arrangements, marital status, income source (i.e., employed/unemployed, student, etc.), the total number of hours per week spent on sedentary behaviors, weight (kg), and BMI (kg/m^2^). Other recorded data includes dieting status, pregnancy status, menopause status, current medical and psychological treatment, and dietary requirements. As part of the detailed face-to-face screening, former and current medical and psychiatric history (via the Structured Clinical Interview DSM-IV; [49]) will also be assessed.

### Pre, post, and follow-up evaluation of the primary and secondary outcomes

#### Primary outcomes

Maladaptive thoughts related to eating and body weight will be assessed at T1, T2, and T3 via the Eating Disorders Beliefs Questionnaire (EDBQ; [50]). The 32-item EDBQ consists of four subscales: (1) negative self-beliefs, (2) weight and shape as a means to acceptance by others, (3) weight and shape as a means to self-acceptance, and (4) control over eating. The instrument has good reliability with a Cronbach’s alpha of 0.93, 0.94, 0.88, and 0.86, for the mentioned subscales, respectively, and good construct validity.

Eating behaviors will be assessed via the Dutch Eating Behavior Questionnaire (DEBQ; [51]). The DEBQ has 33 items clustered in three subscales: (1) restrained eating, (2) emotional eating, and (3) external eating. The subscales of the DEBQ have a high internal consistency and factorial validity with a Cronbach’s alpha of 0.95, 0.94, and 0.80 for the restrained, emotional, and external eating subscales, respectively.

Food cravings will be evaluated via the Trait and State Food Cravings Questionnaires (FCS-S, FCS-T; [52]). The FCS has good psychometric properties and assesses constructs as follows: desire to eat, anticipation of positive reinforcement, anticipation of relief from negative states and post-eating mood, lack of control over eating and craving as a physiological state. The FCS-S consists of 15 items, while the FCS-T consists of 39 items. Both questionnaires have good psychometric properties (Cronbach’s alpha of 0.97 for the FCS-T and 0.94 for the FCS-S).

The Binge Eating Scale (BES; [53]) will be used in order to assess the presence of binge-eating behaviors. The BES consists of 16 items, describing behaviors, emotions, and cognitions surrounding a binge episode (e.g., guilt, fear of not being able to stop eating). The BES was demonstrated to have an excellent internal consistency (Cronbach’s alpha of 0.87; [54]).

In order to assess attentional biases towards healthy and unhealthy food, a modified dot-probe task will be employed [55]. Each trial begins with displaying a fixation cross in the center of the screen for 500 ms, followed by displaying a picture pair for another 500 ms. The relevant pairs consist of pictures of healthy and unhealthy food items and the control/neutral pairs consist of animal pictures. The pictures are displayed on the left and right of the screen, at equal distances from the center. After the pictures disappear, a probe stimulus appears, replacing one of the two images. Participants have to determine as fast as possible whether the probe stimulus replaces the picture on the left or on the right side of the screen by pressing a corresponding key. The order in which the picture pairs are presented will be randomized for all participants.

Attentional bias scores will be calculated by subtracting the mean reaction time to the probes replacing healthy food pictures from the mean reaction time to the probes replacing unhealthy food pictures. Positive scores are indicative of an attentional bias towards healthy food items, while negative scores are indicative of an attentional bias towards unhealthy ones. Reaction times for all the trials will be used to assess attentional biases. Incorrect responses and outlier reaction times will be removed from the analysis.

#### Secondary outcomes

Levels of depression, anxiety, and stress will be evaluated with the Depression, Anxiety, and Stress Scales (DASS; [56]). DASS is a set of three self-report scales designed to measure the negative emotional states of depression, anxiety, and stress and has good psychometric properties (Cronbach’s alpha = 0.96; 0.89; 0.93 for the depression, anxiety, and stress scales, respectively).

The general mood will be evaluated with the Positive and Negative Affect Schedule – Short Form (PANAS-SF; [57]). PANAS has two mood subscales, the positive affect subscale, and the negative affect subscale and has good psychometric properties (Cronbach’s alpha = 0.86 to 0.90).

Weight (kg) and BMI (kg/m^2^) measures will be self-reported via the SIGMA application. Furthermore, physical activity will be assessed via the SIGMA app’s incorporated pedometer and a mean daily step count will be extracted for baseline, post intervention, and follow-up.

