#### Self-monitoring

The self-monitoring module serves two relevant functions, detailed below.

The first function is to assist users in self-monitoring their own eating and physical activity patterns, a proven predictor of weight-loss and weight management [42]. SIGMA includes self-monitoring components aimed at monitoring dietary intake and physical activity, enabling users to plan a meal/menu and physical exercise in advance and offering personalized tips (i.e., psycho-educational content) and feedback regarding eating and physical activity styles.

Aside from planning, the monitoring of physical activity is aided by an embedded *pedometer*. The decision to incorporate a pedometer was informed by the fact that it has been reliably associated with significant increases in physical activity and significant decreases in BMI ([43]). The pedometer will monitor and compare the user’s daily performance with a daily suggested target and will provide feedback and healthy habit points accordingly. As such, a norm of between 5000 and 7499 steps/day is considered low active, 7500 to 9999 steps/day is somewhat active, and 10,000 or more steps/day is considered an active lifestyle [44]).

The second function, drawing on the cognitive-behavioral principles, is to monitor how well the participants apply the CBT principles of the SIGMA game to real-life situations. Hence, a special feature of the monitoring module is the *ABC diary* that focuses on understanding the *A*ntecedents and *C*onsequences of maladaptive *B*eliefs regarding food, weight or the ability to maintain the diet. This should aid the users in noticing and challenging their maladaptive patterns without relying on a therapist for weight management.

Regarding the consequences of eating behaviors, users will be enabled to monitor their levels of reported satiety after a meal, as well as their emotional reactions after eating, such as guilt or satisfaction. Lower levels of satiety and negative emotional reactions after eating may predict a relapse and it is important for the app to offer alternative ways of thinking in tempting or adverse situations. This should help alleviate urges to eat outside planned meals or prevent feelings of guilt when it happens.

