### Outcome measures and evaluation instruments used outside the application

The evaluation of the primary and secondary outcomes will be conducted before the intervention (T0), at post intervention (T1 – after 2 months), and at follow-up (T2 – after 3 months of follow-up). There will also be a constant monitoring of some of the parameters, which will be described in detail below. Most self-reported measurements, except for weight and BMI, will be recorded through the study’s website to ease visibility of multi-item questionnaires. The remaining variables, such as daily steps, attention bias, and all the constantly monitored aspects, are embedded within the mobile platform. Screening and collection of demographic data will be performed during a face-to-face meeting.

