#### Constantly monitored aspects

A special feature of the monitoring module is the *ABC diary*. The *ABC diary* is meant to be filled in (1) at the end of the day after an unplanned meal or after an impulsive eating episode took place or (2) in problematic situations, while still contemplating yielding to eating urges. Hence, the *ABC diary* monitoring tool has two features, as detailed below.

When filled in at the end of the day, the *ABC diary* has an awareness role as users can notice what self-reported emotions, cravings, and sabotaging thoughts preceded and ensued their eating behavior. As such, users can choose from a list of emotions, cravings, and beliefs and rate their intensity, or fill in some of their own. An automatically generated graph indicates whether a change in time occurred in any of these variables and pinpoints to triggering/problematic situations.

When filled in problematic situations, the *ABC diary* has a preventive role. In addition to recording emotions, cravings, and sabotaging thoughts, the *ABC diary* monitoring tool provides healthy alternative ways of thinking/coping tips or allows the user to write some personally motivational healthy statements. If alternative ways of thinking do not decrease the urge or desire to eat, then the user is redirected to the Crisis and Relapse prevention module in an effort to reduce the relapse rate.

The healthy habit points system is another constantly monitored aspect. Within the SIGMA application, there are three possible sources of earning points: (1) the explicit cognitive-behavioral intervention (SIGMAe), (b) the implicit attention-training intervention (SIGMAi), and (c) the pedometer. In SIGMAi and SIGMAe awarded points vary from 0 to 8 healthy habit points. Regarding the pedometer, the points received by the user each day will be proportional to the number of steps taken (i.e., 5 points for 5000 steps, 8 points for 8000 steps, etc.). Furthermore, a calorie counter is also available to keep track of daily calorie consumption. However, the application does not encourage a fixation on calorie counting [45]. Hence, no points are earned for its usage. Overall, the points gathered from SIGMAe, SIGMAi, and the pedometer will be assessed separately, as well as pooled into a total score indicative of overall learning and adherence to the intervention.

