### Data analysis

To test the efficacy of the SIGMA intervention against the attention placebo control group a 2 (group: SIGMA intervention group versus attention placebo group) × 3 (time: pre vs. post vs. follow-up) general linear mixed model will be used with regard to the primary and secondary outcomes. Separate analyses will be performed for the “intent-to-treat” and the completer sample. The intent-to-treat principle will be employed [58] with the last observation carried forward method. The Bonferroni-Holm correction will be used to adjust for multiple comparisons. Overall, with a sample of at least 74 participants, the trial will be powered to identify at least a medium effect size (i.e., Cohen’s *d* = 0.50).

App usage data and user activity will be inspected by contrasting; for example, the participants’ self-reported activity with their actual app usage as recorded in the database. This will inform us about any impediments to user adherence, as well as particular usage patterns.

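### Daily step counts enter the analysis as three means with carry-forward, so on the natural reading a participant who leaves before T1 is scored as unchanged despite recorded treated steps

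*Protocol article*

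**What the plan says.** Steps are captured continuously. Under Self-monitoring, "The pedometer will monitor and compare the user’s daily performance with a daily suggested target". Under Constantly monitored aspects, "the points received by the user each day will be proportional to the number of steps taken". The section on outcome measures places the data in the app: "The remaining variables, such as daily steps, attention bias, and all the constantly monitored aspects, are embedded within the mobile platform".

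For the outcome itself, the Secondary outcomes section reduces this series to three values per participant: "a mean daily step count will be extracted for baseline, post intervention, and follow-up". Apart from baseline, the assessment times are "at post intervention (T1 – after 2 months), and at follow-up (T2 – after 3 months of follow-up"), so no outcome level lies between baseline and two months. The Data analysis section specifies two groups by "3 (time: pre vs. post vs. follow-up) general linear mixed model will be used with regard to the primary and secondary outcomes" and adds: "The intent-to-treat principle will be employed [58] with the last observation carried forward method". Intent-to-treat and completer samples are analysed separately.

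The Sample size section allows for up to 40% dropout, described as a worst case, with 52 randomised per arm. A change in steps is part of the stated secondary hypothesis, and the Discussion names step counts among the more objective supplements to self-report.

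**The concern.** The questionnaires have no values between baseline and T1, so someone who leaves in between has nothing on treatment to analyse. Steps differ: a participant who stops after week 2, 4 or 6 of the eight-week intervention has about 14, 28 or 42 treated days of counts.

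Put together, the three-value extraction, the three time levels and the carry-forward rule mean that none of those days reaches the step analysis. The intent-to-treat analysis replaces them with a pre-treatment mean, which is a change of exactly zero. The completer analysis omits the participant. The only other uses stated for pedometer data are the points score and an inspection of app usage. What is at stake is the size, and possibly the direction, of the group difference in steps.

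**Working it through.** The plan gives no figure for steps, so there is none to reproduce. The check has two parts: the bias from carrying baseline forward, and what a weekly model would gain.

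**1. Bias from carrying baseline forward**

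Let Δ_S and Δ_C be the true mean changes at T1 in the SIGMA and control arms, and q_S and q_C the shares leaving before T1. Assume leaving is unrelated to response. Leavers score zero, so

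expected difference = (1 − q_S)·Δ_S − (1 − q_C)·Δ_C.

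*Equal dropout q.* This is (1 − q) times the true difference. For an assumed true difference of 1,000 steps/day:
- q = 0.10: 900
- q = 0.20: 800
- q = 0.30: 700
- q = 0.40 (the planned maximum, all before T1): 600

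*Unequal dropout*, assumed 20% against 40%:
- Both arms truly gain 1,000 and SIGMA loses fewer: 0.8 × 1,000 − 0.6 × 1,000 = +200, a spurious benefit.
- The same with SIGMA losing more: 0.6 × 1,000 − 0.8 × 1,000 = −200.
- True gains 1,500 and 500 (difference 1,000): 0.8 × 1,500 − 0.6 × 500 = 900 if SIGMA loses fewer, and 0.6 × 1,500 − 0.8 × 500 = 500 if it loses more.

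*Power*, at a true standardised difference of 0.50 on change (SD 1), 52 per arm, two-sided 5%, q = 0.40:
- Difference 0.6 × 0.50 = 0.30.
- Variance of change: SIGMA 0.6 + 0.4 × 0.6 × 0.25 = 0.66; control 0.60.
- SE = √((0.66 + 0.60)/52) = 0.156, and power = Φ(0.30/0.156 − 1.96) ≈ 0.49, against 0.72 with no dropout.
- A t-test in the 31 per arm who remain (52 × 0.6 = 31.2) also has power of about 0.49. Compared with completers, the cost of carry-forward is a distorted estimate, not extra lost power.

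**2. Gain from a weekly model**

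Assumed inputs, none from the documents: between-person SD 2,500; day-to-day SD 3,000; week-to-week SD 500, 1,000 or 1,500 (the three values in each list below); 14-day baseline; 40% dropout spread evenly over weeks 0–7 in both arms; one-week T1 window.

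*Week-8 completers, baseline-adjusted.* With week SD 500:
- Variance of a weekly mean: 2,500² + 500² + 3,000²/7 = 7,785,714.
- Variance of the baseline mean: 2,500² + 500²/2 + 3,000²/14 = 7,017,857.
- Residual variance: 7,785,714 − 2,500⁴/7,017,857 = 2,219,556.
- SE = √(2 × 2,219,556/31.2) = 377.

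For the three week SDs the SE is 377, 457 and 561.

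*Week-8 contrast from the weekly model* (generalised least squares, all recorded weeks, common baseline): SE 363, 441 and 544. The reduction is about 3–4%.

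*Eight-week average from the weekly model* (simulation, 1,500 replicates): SE 207, 240 and 299, against 386, 463 and 572 for week-8 completers in the same runs, so 46–48% smaller. Most of that comes from averaging over more weeks: completers alone with an eight-week mean already reach 237, 283 and 342.

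*Effect building linearly to 1,000 at week 8.*
- Week-8 contrast of the weekly model (simulation): 992 to 1,009.
- Baseline carried forward (simulation): 592 to 601.
- True eight-week average: (125 + 250 + … + 1,000)/8 = 562.5.
- Simple mean of whatever weeks each person recorded: a person with k weeks averages 62.5(k + 1), so (0.6 × 562.5 + 0.05 × 2,187.5)/0.95 ≈ 470, which is further from the T1 effect than carry-forward.

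**The case against.** **The T1 window is undefined.** If the post-intervention mean covered the whole intervention period, an early leaver would have a treated value and the problem would largely disappear. For a variable recorded daily, the last observation could also mean the last recorded days. Both readings are possible. However, T1 is placed after two months and the model has a single post level, so a mean at the end of treatment is the natural reading. Leaving the window to the full protocol is not itself a fault.

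**This is the general objection to carry-forward.** Partly so: the proportional shrinkage applies to every outcome in the model. Steps differ in that recorded treated values exist and are overridden.

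**Stronger claims that a reader might infer do not hold:**
- *That using all weeks nearly halves the standard error.* That belongs to the eight-week average, a different estimand. For the T1 contrast the gain is about 3–4% against a one-week window. If T1 were a 14-day window matching baseline, the completer SE would be 305, 368 and 449, below the weekly model's single-week contrast.
- *That the step effect is always pulled toward zero.* Only equal, non-informative dropout guarantees this.
- *That 40% is the expected loss.* The article calls it a worst case and does not say how much falls before T1.
- *That steps are the only variable with recorded data between visits.* The ABC diary also logs emotions, cravings and thoughts, although it is not one of the outcome instruments.
- *That the daily series is certainly on a server.* The article mentions locally stored data, secure transfer and a usage database, but does not say that daily steps are uploaded and kept.

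**Conclusion.** The point holds in limited form. The plan fixes a three-value extraction and a carry-forward rule that, on the natural reading, replace recorded treated steps with a pre-treatment mean for anyone who leaves before T1; the completer analysis does not use those steps either. With equal, non-informative dropout the estimate is too small by the share leaving before T1, at most 40% under the planned worst case. With unequal dropout it can err in either direction, including a spurious 200 steps/day when both arms truly gain 1,000 and dropout is 20% against 40%.

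The benefit of changing the method is chiefly a less biased T1 estimate, not a more precise one. The bias figures rest on leaving being unrelated to response and on a participant's step record ending when they leave; someone who stops treatment but keeps the app running could still have a T1 mean. The precision figures rest on the assumed variances. This is an improvement worth making to a named secondary outcome; it does not threaten the trial's primary conclusions.

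**What to change.** In the Secondary outcomes and Data analysis sections:
- Analyse weekly mean steps as the repeated measure in the mixed model, using every recorded week, with no carry-forward for this outcome.
- Take the group contrasts at the last intervention week (T1) and the last follow-up week (T2).
- Report the eight-week intervention average alongside, labelled as a separate estimand, because it understates the T1 effect if the effect builds up.
- State the window that defines T1 and T2. If two weeks were intended, to match baseline, take the contrast from the same model over those two weeks.
- Keep the three window means as a descriptive table if wanted.

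The cost is revised wording and a little more programming, provided the daily or weekly counts are retained, which the sponsor should confirm. Steps will have more time levels than the other outcomes. The model relies on data being missing at random after a participant stops, so informative stopping remains a limitation.

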#### Constantly monitored aspects

A special feature of the monitoring module is the *ABC diary*. The *ABC diary* is meant to be filled in (1) at the end of the day after an unplanned meal or after an impulsive eating episode took place or (2) in problematic situations, while still contemplating yielding to eating urges. Hence, the *ABC diary* monitoring tool has two features, as detailed below.

When filled in at the end of the day, the *ABC diary* has an awareness role as users can notice what self-reported emotions, cravings, and sabotaging thoughts preceded and ensued their eating behavior. As such, users can choose from a list of emotions, cravings, and beliefs and rate their intensity, or fill in some of their own. An automatically generated graph indicates whether a change in time occurred in any of these variables and pinpoints to triggering/problematic situations.

When filled in problematic situations, the *ABC diary* has a preventive role. In addition to recording emotions, cravings, and sabotaging thoughts, the *ABC diary* monitoring tool provides healthy alternative ways of thinking/coping tips or allows the user to write some personally motivational healthy statements. If alternative ways of thinking do not decrease the urge or desire to eat, then the user is redirected to the Crisis and Relapse prevention module in an effort to reduce the relapse rate.

The healthy habit points system is another constantly monitored aspect. Within the SIGMA application, there are three possible sources of earning points: (1) the explicit cognitive-behavioral intervention (SIGMAe), (b) the implicit attention-training intervention (SIGMAi), and (c) the pedometer. In SIGMAi and SIGMAe awarded points vary from 0 to 8 healthy habit points. Regarding the pedometer, the points received by the user each day will be proportional to the number of steps taken (i.e., 5 points for 5000 steps, 8 points for 8000 steps, etc.). Furthermore, a calorie counter is also available to keep track of daily calorie consumption. However, the application does not encourage a fixation on calorie counting [45]. Hence, no points are earned for its usage. Overall, the points gathered from SIGMAe, SIGMAi, and the pedometer will be assessed separately, as well as pooled into a total score indicative of overall learning and adherence to the intervention.

### Data analysis

To test the efficacy of the SIGMA intervention against the attention placebo control group a 2 (group: SIGMA intervention group versus attention placebo group) × 3 (time: pre vs. post vs. follow-up) general linear mixed model will be used with regard to the primary and secondary outcomes. Separate analyses will be performed for the “intent-to-treat” and the completer sample. The intent-to-treat principle will be employed [58] with the last observation carried forward method. The Bonferroni-Holm correction will be used to adjust for multiple comparisons. Overall, with a sample of at least 74 participants, the trial will be powered to identify at least a medium effect size (i.e., Cohen’s *d* = 0.50).

App usage data and user activity will be inspected by contrasting; for example, the participants’ self-reported activity with their actual app usage as recorded in the database. This will inform us about any impediments to user adherence, as well as particular usage patterns.

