#### Sample size

In order to detect a medium effect size (i.e., Cohen’s *d* = 0.50), with a *p* ≤ 0.05 and 80% power, we would need a total of 74 participants, 37 participants per arm (calculated using G*Power, [48]). Assuming that up to 40% of participants will drop out of the intervention [16], a total of 104 participants will be needed (52 participants per trial arm) in order to detect the aforementioned effect size. The 40% percentage dropout rate represents the worst-case scenario as a high dropout rate can be sometimes expected in mHealth or eHealth studies [16].

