#### Randomization and blinding

Selected participants will be randomized in the intervention and control trial arms in a 1:1 ratio (Fig. 5). An independent researcher will handle the randomization and the random sequence will be generated using a 1:1 allocation ratio via an online available random number generator (i.e., https://www.random.org/). More specifically, randomization will be prestratified by gender and follow a permuted-block randomization scheme to ensure a balance between the arms of the trial.

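### Fitting the pre-treatment score as a free time level turns each arm comparison into a change-score comparison; adjusting for the T0 score already collected would be more precise at no cost

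*Protocol article*

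**What the plan says.** The Data analysis section sets one model for every outcome: two groups crossed with "3 (time: pre vs. post vs. follow-up) general linear mixed model will be used with regard to the primary and secondary outcomes". Pre-treatment is therefore one of the three levels of the response. The section mentions neither a baseline covariate nor a common baseline mean, and its only factors are group and time. It names no term or contrast of the model as the efficacy test, and no primary time point.

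The section on outcome measures used outside the application says that the evaluations "will be conducted before the intervention (T0), at post intervention (T1 – after 2 months), and at follow-up (T2 – after 3 months of follow-up", so a T0 value is planned for the primary and secondary outcomes.

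Under Randomization and blinding, "Selected participants will be randomized in the intervention and control trial arms in a 1:1 ratio", and "randomization will be prestratified by gender and follow a permuted-block randomization scheme".

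The Sample size section plans "In order to detect a medium effect size", Cohen's d = 0.50, and states: "≤ 0.05 and 80% power, we would need a total of 74 participants, 37 participants per arm". After the dropout allowance, "a total of 104 participants will be needed (52 participants per trial arm". The section on the trial's aims expects the benefit to persist at follow-up.

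**The concern.** T0 is measured before treatment starts, so randomisation makes the true arm difference there zero. A full 2 x 3 model does not use this. It estimates a separate T0 difference and, in a comparison of arms at T1 or T2 relative to T0, subtracts it. That carries the full noise of the T0 measurement into the treatment estimate. Using T0 as a covariate subtracts only the part that predicts the later score.

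Precision is at stake, not bias. Both approaches estimate the same treatment effect under randomisation, but one needs more participants for the same power. The trial is small, and Bonferroni-Holm correction across several outcomes leaves less alpha for each test, so precision available from data already collected is worth taking.

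**Working it through.** **Inputs.** d = 0.50 with SD set to 1, 37 per arm, and 52 per arm as the inflated size (Sample size section); 1:1 allocation; the effect present at T1 and equal at T2, which is the article's hypothesis. Assumed, because the article does not give them: two-sided 0.05, equal correlation rho between all pairs of visits (compound symmetry), complete data, and rho from 0.3 to 0.8.

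**The plan's own figure.** A two-sample t-test with d = 0.50 and 80% power needs 64 per arm (128 in total) two-sided, or 51 per arm (102) one-sided. Neither gives 74. At 37 per arm, a two-sided t-test on the T1 score alone has 56% power. The origin of 74 is a separate matter and adds no weight here; 37 per arm serves only as a common basis for comparing the two analyses.

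**Variance of the T1 arm contrast.** With n per arm it is (2/n) times a factor:
- T0 as a free level (change score): 2(1-rho)
- T0 as covariate, or common T0 mean: 1-rho²
- Ratio, adjusted to change: (1-rho²) / [2(1-rho)] = (1+rho)/2

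The ratio is 0.65, 0.75, 0.85 and 0.90 at rho 0.3, 0.5, 0.7 and 0.8, so the variance falls by 35%, 25%, 15% and 10%. Below rho 0.5 the change-score factor exceeds 1, so the change contrast is then less precise than ignoring T0 altogether.

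**Power at T1.** Noncentrality = d·√(n/2) / √factor. With n = 37, d·√(n/2) = 0.50 × √18.5 = 2.151. At rho 0.5 this gives 2.151/√1.00 = 2.151 for change (72 df) and 2.151/√0.75 = 2.483 for adjusted (71 df).

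**The 2-df group x time term, if that is the test.** With an effect of d at both T1 and T2, the noncentrality is n·d² / [3(1-rho)]. At rho 0.5 it is 37 × 0.25 / 1.5 = 6.17, referred to F(2, 144).

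**The adjusted mean of T1 and T2.** The factor is (1+rho)/2 - rho², which is 0.50 at rho 0.5.

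Power at 37 per arm:

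| rho | T1 change, 1 df | T1 adjusted, 1 df | group x time, 2 df | adjusted mean of T1 and T2, 1 df |
|---|---|---|---|---|
| 0.3 | 43% | 60% | 44% | 81% |
| 0.5 | 56% | 69% | 59% | 85% |
| 0.7 | 78% | 84% | 82% | 94% |
| 0.8 | 92% | 94% | 95% | 99% |

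The last column combines two gains, baseline adjustment and averaging of two visits, and it relies on the effect being fully maintained.

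At 52 per arm, T1 change against T1 adjusted is 57% and 75% (rho 0.3), 71% and 83% (0.5), 90% and 94% (0.7), 98% and 99% (0.8).

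Total N for 80% power at T1, change against adjusted: 178 and 118 (rho 0.3), 128 and 98 (0.5), 78 and 68 (0.7), 54 and 48 (0.8).

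**Gender.** In the stated model, a gender effect that is constant over time is the same in a person's T0 and T1 scores and cancels from the change. With complete data, adding it leaves the group x time standard error as it was. In a simulated check with 52 per arm and a real gender effect, the standard error was 0.1949 with and without the term. In the baseline-adjusted model it can help a little: at rho 0.5 and 37 per arm, power at T1 moves from 69% to 70%, 71% or 73% if gender explains 2%, 5% or 10% of the residual variance (assumed values).

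**The case against.** The strongest reply is that a group-by-time repeated-measures model is standard and valid under randomisation, and that nothing in the article contradicts it. A journal article may leave covariates and contrasts to the analysis plan, and the Bonferroni-Holm correction leaves room for follow-up contrasts. The gain also depends on a correlation that nobody has stated. Much of this stands. The issue is efficiency, and at rho 0.8 the gain at T1 is 2 points of power. But the placing of the pre-treatment score among the outcome levels is stated, not left open, and adjustment is more precise at every rho below 1. The Abstract's description of the outcomes as changes is no obstacle: under randomisation, the adjusted arm difference and the difference in change estimate the same quantity.

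Three stronger readings are tempting, and the document does not support them:
- **That the plan tests an omnibus interaction, and that this test wastes power.** The article names no term. If the 2-df term is the test, it is no worse than the 1-df change contrast at T1 under a sustained effect (59% against 56% at rho 0.5). The loss comes from the free baseline. Low power of the group main effect is likewise no finding, since the article does not propose that test.
- **That leaving out gender makes the stated model's standard errors too large.** A constant gender effect cancels from its within-person contrasts. Last observation carried forward fills the intent-to-treat data, and completers are complete by definition, so this holds in both planned analyses.
- **That the shortfall against the stated 80% power makes this point more serious.** That is a sample-size question in its own right.

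**Conclusion.** The point holds as one of efficiency. With the pre-treatment score as a free level, the post-baseline arm contrasts are change-score contrasts, and the T0 data would give a variance smaller by the factor (1+rho)/2. At 37 per arm the gain in T1 power is 17 points at rho 0.3 (60 - 43), 13 at 0.5 (69 - 56), 6 at 0.7 (84 - 78) and 2 at 0.8 (94 - 92). Against the 2-df group x time term, if that is the intended test, the adjusted T1 contrast gains 16, 10 and 2 to 3 points at rho 0.3, 0.5 and 0.7, and nothing at 0.8.

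These figures rest on compound symmetry, complete data, an unadjusted two-sided 0.05 and an assumed rho. Multiplicity correction lowers all of them: at rho 0.5 and a first Holm step of 0.05/3, for the three primary domains in the Abstract, power is 39% for change and 52% for adjusted. Baseline adjustment alone does not bring a single T1 contrast to 80% at 74 participants unless rho is about 0.65 or more (total N 76 at 0.65, 98 at 0.5).

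The stated analysis is not biased or invalid. It is a worthwhile change, not a critical one.

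**What to change.** In the Data analysis section, replace the 2 x 3 model by one of two forms:
- a mixed model with T1 and T2 as outcomes and fixed effects for T0 score x time, group x time and gender; or
- a constrained longitudinal model on T0, T1 and T2 with a common T0 mean for both arms, and gender.

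Gender belongs in the model because randomisation is stratified by it; the expected gain is small. Base the efficacy claim on one pre-specified 1-df arm contrast, either at T1 or on the mean of T1 and T2, reported with a 95% confidence interval. The mean is the more powerful choice only if the effect is expected to last, as the article hypothesises. State the assumed correlation between visits next to the sample size, so that the power of the chosen contrast can be checked.

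The cost is wording. T0 scores and gender are already collected, no visit or measurement is added, and the article gives the trial status as recruiting, so the change can be made and recorded with the registry before the data are unblinded.
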